## Abstract

**Background:**

Alcohol abuse comes with risks for increased morbidity and mortality among patients with HIV. This study aims to determine the prevalence of alcohol use and other risk factors in a sample of primary care patients with HIV in South Africa and to assess a brief intervention to reduce the use of alcohol in this group.

**Methods/Design:**

A single-blinded randomized controlled trial is designed to determine the efficacy of a brief intervention to reduce hazardous alcohol use in patients with HIV. The study will be carried out on out-patients with HIV in two primary healthcare HIV clinics near Pretoria, South Africa. Alcohol use will be assessed with the Alcohol Use Disorder Identification Test questionnaire. Other data that will be collected relate to health-related quality of life, depression, sexual behavior, internalized AIDS stigma, HIV-related information and adherence to antiretroviral therapy (self-reported 7-day recall of missed doses, Visual Analog Scale and pill count). The intervention consists of a brief counseling session to reduce alcohol risk; the control group receives a health education leaflet.

**Discussion:**

The findings will be important in the public health setting. If the intervention proves to be efficient, it could potentially be incorporated into the HIV care policy of the Ministry of Health.

**Trial registration:**

Pan African Clinical trial Registry: PACTR201202000355384

## Background

The use of alcohol in South Africa is among the highest in Africa
[1] with a total adult per-capita consumption of 9.5 l pure alcohol per year, and a consumption of 34.91 l pure alcohol per year (men 39.64 l, women 23.84 l) among people that drink alcohol
[2]. Since South Africa also has one of the highest prevalences of HIV in the world (prevalence estimated to be 17.8% among adults aged 15 to 49 in 2009)
[3], it is possible that a considerable number of persons living with HIV engage in hazardous or harmful alcohol use. Hazardous drinking is defined as a quantity or pattern of alcohol consumption that places patients at risk for adverse health events, while harmful drinking is defined as alcohol consumption that results in adverse events (for example, physical or psychological harm)
[4]. Prevalence data on (hazardous) alcohol use in patients with HIV in Africa vary since different measuring tools were used in different study populations. A systematic review by Nakimuli-Mpungu and colleagues on alcohol use, depression and adherence to antiretroviral therapy (ART) in patients with HIV showed a prevalence of alcohol use between 2.5 and 51%. The prevalence of alcohol use disorders ranged from 2.5 to 31%
[5]. Myer and colleagues reported a prevalence of alcohol dependence/abuse of 7% in patients with HIV in Cape Town
[6].

Studies in several African countries have shown a causal link between alcohol use and HIV, and have shown that alcohol use has effects on the course of HIV, including adherence to ART. The prevalence of HIV is considerable higher in adults who have a history of alcohol consumption or frequently use alcohol than in adults who do not use alcohol
[7-10]. A systematic review and meta-analysis by Fisher and colleagues confirmed the strong association between alcohol use and HIV infection
[11].

The negative effects of alcohol use on the individuals are numerous. High alcohol use is associated with high-risk sexual behavior and risk of HIV
[12,13]. Once individuals are infected with HIV, alcohol use is related to low participation in prevention mother-to-child transmission (PMTCT), pre-test and post-test counseling (including returning for test results)
[14,15]. Overall, there is a late presentation to HIV care in patients that use alcohol, compared with those that do not use alcohol (odds ratio = 3.55, 95% confidence interval = 1.63 to 7.71)
[16]. Adherence to ART is poor if alcohol is used
[17-21].

HIV disease progression is accelerated by alcohol use, which is shown by a more likely decline of CD4 T cells to ≤200 cells/μl and a more frequent detectable viral load in frequent alcohol users, independent of baseline CD4 cell count and HIV viral load, ART use over time, the time since HIV diagnosis, and age and gender
[22-24]. Alcohol use can cause liver problems, which could add to the risk of toxicity in patients using ART.

Screening and brief intervention for alcohol reduction in primary care patients has proven effective in reducing alcohol consumption at 6 and 12 months
[25]. Results from studies on screening and brief intervention in HIV patients using alcohol, mainly performed in the USA, are not conclusive. One study performed in New York showed improvement in self-report and biological markers (CD4 cell count and HIV viral load) after an eight-session behavioral intervention after 3 months. However, this result was not sustained at 6 months
[26]. A multicomponent (including behavioral) intervention showed no significant differences in adherence, CD4 count, viral load or alcohol consumption
[27].

Very few reports from resource-limited settings have been published on interventions to reduce alcohol use in HIV-positive patients. One study describes an intervention based on a culturally adapted, six-session (over a 3-month period) cognitive-behavioral therapy to reduce alcohol use among HIV-infected outpatients in western Kenya, whereby the percentages of days abstinent from alcohol before session 1 were 52 to 100% for women and 21 to 36% for men. By session 6 this was 96 to 100% for women and 89 to 100% for men. The percentages of days abstinent from alcohol effect sizes (Cohen’s *d*) between the first and last cognitive-behavioral therapy sessions were 2.32 for women and 2.64 for men
[28].

This study will measure the prevalence of alcohol use in patients with HIV and assess the efficacy of a brief intervention to reduce alcohol use among selected patients.

## Methods/Design

### Design

The first part of the study will be a screening phase to estimate the prevalence of (hazardous and harmful) alcohol use in the study population. The study design for the efficacy study is a single-blinded randomized controlled trial where information will be collected from patients at inclusion (before the intervention, which is performed in the same session: pre-intervention) and at follow-up of 3 and 12 months.

### Setting, study population and participants

The sample will include out-patients with HIV at the primary care clinics in townships in Gauteng, South Africa. Out-patients with HIV will be screened for hazardous and harmful alcohol use. Patients identified as hazardous drinkers (on the Alcohol Disorder Identification Test (AUDIT) questionnaire) will be randomized into an intervention group or a control group.

### Aim of the study

The aim of the study is to assess the prevalence and severity (hazardous and harmful) of alcohol use in patients with HIV and its associated factors, and to study the efficacy of a brief intervention for hazardous alcohol use in out-patients with HIV in primary health care clinics in townships in South Africa.

### Objectives

The objectives of the screening phase are: to measure the prevalence of alcohol consumption among out-patients with HIV; and to describe drinking patterns, health status, quality of life, sexual behavior and adherence levels among out-patients with HIV, and identify hazardous drinkers needing intervention.

The objectives of the intervention phase are: to compare the level of alcohol consumption, health status, quality of life, level of adherence to ART and sexual behavior among hazardous drinkers between pre-intervention and 3 and 12 months after the intervention; and to compare levels of and changes in alcohol consumption, adherence level to ART, quality of life, health status and number of patients with virological and immunological failure, between intervention and control groups at 3 and 12 months.

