### Inclusion criteria

Patients who are 18 years and older, with HIV-1 infection and who are visiting selected outpatient clinics for their HIV care will be eligible for this study. Patients with hazardous alcohol use will be selected using the AUDIT questionnaire (hazardous drinkers score 8 to 19 for men and 7 to 19 for women).

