### Procedure

All consecutive HIV-positive patients visiting two out-patient clinics will be asked to provide informed consent to receive a baseline assessment (using the data collection instruments) and screening for alcohol problems. If eligible – meaning an AUDIT questionnaire score of 8 to 19 for men or 7 to 19 for women – a second informed consent will be asked before randomization into the intervention or control group. Patients with a score of 20 and above on the AUDIT (with probable alcohol dependence) will be referred for further management (according to local standard procedures). The research assistant nurse will randomize patients by checking the random numbers that allocate the case to the intervention arm or control arms. The intervention or control procedures will be carried out in all patients, after which they will be followed up at 3 and 12 months (which are standard visit intervals for the follow-up of the HIV care). The research assistant performing the follow-up assessments will be blinded to the intervention allocation of the participant. In the event of a drop-out, at least six individual attempts will be made to contact patients by telephone and letter. Even if a contact was not successful at either follow-up point, further attempts will be made at any next follow-up point. Sampling will occur throughout all hours of clinic operation over a 3-month period. Patients will be offered a drink (soda, juice) during the interviews.

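### As written, sexual behavior is compared only before versus after the intervention, so the randomized control arm is not used for it

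*Protocol article*

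**What the plan says.** The Objectives section of the protocol article gives two objectives for the intervention phase.

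- The first takes sexual behavior, ART adherence, quality of life, health status and drinking, and compares them "among hazardous drinkers between pre-intervention and 3 and 12 months after the intervention". No control group enters this comparison.
- The second compares the arms on the level of, and change in, drinking and ART adherence, and on "quality of life, health status and number of patients with virological and immunological failure, between intervention and control groups at 3 and 12 months". Sexual behavior is not in this list.

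The Sexual behavior section, under the data collection instruments, says its questions serve to look at hazardous drinkers before and after the intervention. It does not mention the arms.

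On selection, the Inclusion criteria state that "hazardous drinkers score 8 to 19 for men and 7 to 19 for women". Under Procedure, patients consent "to receive a baseline assessment (using the data collection instruments) and screening for alcohol problems" in one step, and no second AUDIT is described between selection and randomization. The same section says: "Patients with a score of 20 and above on the AUDIT (with probable alcohol dependence) will be referred for further management".

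The Hypothesis is between arms for drinking. The Data analysis section plans a 2×3 repeated-measures model for the alcohol score, aimed at the treatment-by-time interaction. It also plans t and chi-square tests between groups, without naming outcomes. The questionnaires are given at baseline and at each follow-up visit.

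**The concern.** A before-after difference in one group mixes the intervention effect with everything else that changes over 3 to 12 months: secular trend, the effect of being screened and asked, and repeated interviewing on a sensitive topic. The control arm exists to remove these. An outcome that appears only in the before-after objective does not get that benefit, although both arms supply the data. At stake is the reading of one secondary outcome: a change in reported sexual behavior could not be attributed to the counseling.

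The before-after objective has a further weakness for AUDIT. Patients enter because their AUDIT was high, and that same score is the pre-intervention value. On a scale that is not perfectly repeatable, a group chosen this way is expected to score lower on re-measurement without treatment. The objective is not labelled as descriptive, so the document does not warn the reader about this.

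**Working it through.** **1. The two outcome lists side by side**

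| Outcome | First objective (before vs after) | Second objective (between arms) |
|---|---|---|
| Alcohol consumption | yes | yes |
| Health status | yes | yes |
| Quality of life | yes | yes |
| ART adherence | yes | yes |
| Sexual behavior | yes | **no** |
| Virological and immunological failure | no | yes |

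Sexual behavior is the only outcome in the first list that is absent from the second.

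**2. What each contrast estimates**

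Let d be the intervention effect and c the change that would occur in both arms anyway. The arms are equal in size (120 each).

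- Before-after in the intervention arm: c + d.
- Before-after in all randomized patients: c + d/2.
- Between-arm difference in change: (c + d) − c = d.

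Only the last isolates d. This holds for sexual behavior whatever its scale, and needs no assumption about c.

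**3. How large c could be for AUDIT**

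Planned effect, from the Sample size calculation: 12 − 10.6 = 1.4 points. 1.4/12 = 11.7%, which the article gives as 12%.

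The clinic-wide mean μ and the retest correlation r are not in the document, so both are assumed. A simple linear approximation for a selected mean of 12 is: expected fall = (1 − r)(12 − μ).

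- μ = 6, r = 0.9: 0.1 × 6 = 0.6.
- μ = 5, r = 0.8: 0.2 × 7 = 1.4.
- μ = 5, r = 0.6: 0.4 × 7 = 2.8.

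A simulation then applied the upper limit of 19. Scores were normal, rounded and floored at 0, with selection at 8 to 19 for everyone (the women's lower limit of 7 was not modelled), no treatment effect and no trend. Mean and SD refer to the score before rounding and flooring. Mean fall in points:

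| Assumed clinic mean/SD | r = 0.6 | 0.7 | 0.8 | 0.9 |
|---|---|---|---|---|
| 3/5 | 2.84 | 2.16 | 1.46 | 0.74 |
| 4/6 | 2.73 | 2.08 | 1.41 | 0.72 |
| 5/6 | 2.42 | 1.85 | 1.26 | 0.64 |
| 5/7 | 2.54 | 1.96 | 1.33 | 0.68 |
| 8/6 | 1.55 | 1.18 | 0.80 | 0.41 |

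The range is about 0.4 to 2.8 points. The settings whose selected baseline mean lies nearest the article's 12 are 8/6 (about 12.0) and 5/7 (about 11.7); there the fall runs from 0.41 to 2.54. Under every setting the same fall is expected in both arms, so the expected between-arm difference in change is 0.

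**4. Sexual behavior**

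No regression can be computed. Patients are not selected on it, and the article does not give its questions or scoring. The argument for this outcome is step 2 alone.

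**The case against.** The strongest reply is that the plan already handles this where it matters. Four of the five outcomes have a between-arm objective, the hypothesis says the intervention arm will reduce drinking more than the control arm, and the alcohol model targets the interaction. Regression to the mean is equal in expectation in both arms and cancels there. No paired or before-after test is named, and nothing says that a within-group fall will count as efficacy. The first objective can be read as describing change over time, with the second as the causal comparison. All of this stands.

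It follows that several stronger inferences fail:

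- A reader might infer that the efficacy result on alcohol rests on an uncontrolled comparison. It does not.
- A reader might infer that regression alone would equal the planned effect. That comes from choosing particular values, such as a clinic mean of 5 and a correlation of 0.8. The fall is expected rather than certain, and its size is unknown.
- A reader might carry the AUDIT figures over to sexual behavior. Nothing in the document supports that.

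It can also be said that the unnamed t and chi-square tests may cover sexual behavior, that no hypothesis is stated for it, and that an article condenses a fuller protocol. So it would be wrong to conclude that no between-arm analysis is intended. But no section assigns one, and two separate sections frame this outcome as before and after. That part of the point remains.

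**Conclusion.** The point holds in a narrow form. Under the stated objectives, sexual behavior gets an uncontrolled comparison although it is collected in both randomized arms. This conclusion rests on the text alone.

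The AUDIT calculation is a supporting reason to label before-after change as descriptive. The no-effect fall of about 0.4 to 2.8 points, against a planned 1.4, depends on the assumed correlations of 0.6 to 0.9 and clinic means of 3 to 8. The sample size and the main efficacy test are unaffected. Severity is low; this is a free improvement.

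**What to change.** Make two changes to the Objectives.

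1. Add sexual behavior to the between-arm objective at 3 and 12 months, adjusted for its baseline value, with a model suited to how the questions are scored.
2. State that before-after change is descriptive, is reported separately by arm, and is not evidence of efficacy.

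The first objective need not otherwise be rewritten, because turning it into a between-arm comparison would duplicate the second. The cost is a few words, one sentence and one more row in the between-arm results. No extra data, visits or patients are needed, since the questionnaires are already given at baseline and at every follow-up.

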### Hypothesis

Hazardous drinkers with HIV in the intervention group will reduce alcohol drinking more than those in the control group. In patients that reduce alcohol use, a positive effect will be seen in adherence levels to ART, quality of life, health status and virological and immunological response.

### Inclusion criteria

Patients who are 18 years and older, with HIV-1 infection and who are visiting selected outpatient clinics for their HIV care will be eligible for this study. Patients with hazardous alcohol use will be selected using the AUDIT questionnaire (hazardous drinkers score 8 to 19 for men and 7 to 19 for women).

### Exclusion criteria

Patients with mental impairment, patients already undergoing alcohol reduction treatment and pregnant women will be excluded from this study.

### Sample size calculation

The sample size was calculated using Open Epi
[29]. Based on the current AUDIT score of 12 among HIV patients, it is assumed that the intervention will reduce the current AUDIT score by 12% to 10.6
[30,31]. Based on this assumption, the estimated sample size will allow us with 80% power (5% level of significance) to detect the difference of 12% between the two groups. This will give a minimum of 99 patients per arm. It is expected that 20% of participants may be lost prior to completing the 3-month and 12-month follow-up assessments so that the final sample would be 120 per arm. A total of 240 HIV patients (with AUDIT scores 8 to 19 for men or 7 to 19 for women) will be recruited for the study.

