### Interventions

#### Control group

Patients in the control group will only receive a health education leaflet on responsible drinking. They will receive the brief intervention only after 12-month follow-up, if the intervention has proven to be successful.

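### The 80% power treats the assumed fall from the current AUDIT score (12 to 10.6) as the between-arm difference, gives no SD, and is not met by the 96 completers per arm that the plan expects

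*Protocol article*

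**What the plan says.** All of the inputs are in the protocol article under Sample size calculation.

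- Starting level: "Based on the current AUDIT score of 12 among HIV patients".
- Assumed effect: "it is assumed that the intervention will reduce the current AUDIT score by 12% to 10.6".
- Target of the power statement, which the article derives from that assumption: 80% power at the 5% level "to detect the difference of 12% between the two groups".
- Result: "This will give a minimum of 99 patients per arm".
- Attrition: "It is expected that 20% of participants may be lost prior to completing the 3-month and 12-month follow-up assessments". The final number is 120 per arm, 240 in total.

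The section states neither an SD nor whether the test is one- or two-sided.

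Two other sections bear on how controls may behave. Inclusion criteria select on the outcome scale itself ("hazardous drinkers score 8 to 19 for men and 7 to 19 for women"). Under Control group, "Patients in the control group will only receive a health education leaflet on responsible drinking"; the Intervention group section shows that the leaflet is also part of the intervention. The Hypothesis section predicts a larger reduction in the intervention arm than in controls, so some change in controls was contemplated.

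**The concern.** A fall from the current score and a difference between arms at follow-up are different quantities. The sample size section moves from the first to the second without saying how they are linked. They are equal only if controls average exactly 12 at follow-up, or if the 12% is already net of whatever happens to controls.

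The SD matters just as much. Without it, nobody can reproduce the 99 or judge whether the assumed spread is reasonable.

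At stake is what the 80% means. It is the figure that justifies recruiting 240 patients, and as written it rests on one condition that is left implicit and one input that is missing. The attrition step then leaves fewer completers than the stated minimum.

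**Working it through.** **Inputs from the protocol article:** current mean 12; assumed level 10.6; power 80%; alpha 5%; 99 per arm before attrition; 20% loss; 120 per arm recruited. **Assumed here:** two-sided test, equal allocation, comparison of two means at one follow-up.

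**1. Difference.** 12 − 10.6 = 1.4 points. The unrounded 12% of 12 is 1.44.

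**2. The plan's 99.** It cannot be reproduced from the stated inputs because the SD is missing, so the SD is back-solved:

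SD = difference × √(n/2) / (1.960 + 0.8416)

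- Difference 1.4: 1.4 × √49.5 / 2.8016 = 3.52
- Difference 1.44: 1.44 × √49.5 / 2.8016 = 3.62

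Either way the standardised difference is 0.40. Going forward with SD 3.5: n = 2 × 2.8016² × 3.5² / 1.4² = 98.1, rounded up to 99. SD 3.6 with 1.44 gives the same. A one-sided test would imply 3.96 or 4.07, but the article does not claim one.

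**3. Attrition.** 120 × 0.80 = 96, below 99. The 120 is close to 99 × 1.2 = 119; keeping 99 after a 20% loss needs 99 / 0.8 = 124.

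**4. Power at 96 per arm.** Noncentrality = 1.4 / (3.5 × √(2/96)) = 2.77. Power is 79% by noncentral t, and also 79% by the normal approximation. At 99 per arm it is 80%, so attrition alone costs about one percentage point.

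**5. What the two readings imply.** Suppose, as an illustration, that controls fall by 0.5 points.

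| Reading | Control mean | Intervention mean | Difference |
|---|---|---|---|
| 1.4 is net of control change | 11.5 | 10.1 | 1.4 |
| 10.6 is the intervention arm's total follow-up level | 11.5 | 10.6 | 0.9 |

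Only the second reading loses power.

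**6. Sensitivity at 96 per arm (two-sided 5%, noncentral t).** The adjusted column multiplies the SD by √(1 − 0.5²) = 0.866, for an assumed correlation of 0.5 between baseline and follow-up. The 0.9-point difference, the SDs of 4.0 and 5.0 and the correlation are assumptions; the article gives none of them.

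| Net difference | Follow-up SD | Noncentrality, unadjusted / adjusted | Power, unadjusted | Power, adjusted |
|---|---|---|---|---|
| 1.4 | 3.5 | 2.77 / 3.20 | 79% | 89% |
| 0.9 | 3.5 | 1.78 / 2.06 | 43% | 53% |
| 1.4 | 4.0 | 2.42 / 2.80 | 67% | 80% |
| 1.4 | 5.0 | 1.94 / 2.24 | 49% | 61% |

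**The case against.** The strongest reply is that a net-effect reading is available. A reduction that the intervention brings about can mean the part attributable to it, and the next sentence calls the 12% a difference between groups. Whether the figure was control-adjusted depends on the cited sources, which are not at hand. This stands as a possible reading. It does not settle the matter, because the text ties 10.6 to the current score and not to a control follow-up mean.

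A reader might go further and infer that controls are bound to fall, through regression to the mean, screening and the leaflet, and that the trial is therefore underpowered. The document does not support that. Both arms are selected on the same window, assessed alike and given the leaflet. Under randomisation such shared falls largely cancel, and an additive effect of 1.4 points survives them.

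A reader might also infer that an SD of 3.5 is too small. It is close to the SD of a uniform spread over 8 to 19 (3.45) and a little below that over 7 to 19 (3.74). Follow-up scores are not confined to the entry window, so a larger SD is plausible, but the article contains nothing that shows it.

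It is also fair to say that an unadjusted comparison at one time point is not the planned analysis, which is a repeated-measures model using baseline, 3 and 12 months. Using the baseline could recover much of the loss: with a correlation of 0.5, SD 4.0 gives 80%. It cannot restore a difference that control change has removed; the 0.9-point case reaches only 53%.

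Finally, a condensed article may leave a sensitivity table to the full protocol. That is fair for the table, but not for a power statement whose stated basis equates two different quantities.

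**Conclusion.** The point holds as one about what the power statement is conditional on. As written, 80% requires an unchanged control mean of 12, or a net effect of 1.4 points that the text does not declare. It also requires an SD of about 3.5 (3.6 for a 1.44-point difference), which is unstated and is recovered here on the assumption of a two-sided test. On those same inputs the 96 expected completers give about 79%, so the certain numerical error is small.

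The larger losses depend on conditions that the document does not establish: that 10.6 is the intervention arm's total follow-up level while controls also fall, or that the follow-up SD exceeds 3.5. It would be wrong to conclude that the trial is shown to be underpowered. A reader might likewise expect a null result to be taken as firm evidence of no effect, but nothing in the article says it would be read that way.

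**What to change.** Restate the calculation along these lines: *96 evaluable patients per arm give about 79% power (two-sided 5%) for a between-arm difference of 1.4 AUDIT points at follow-up, net of any change in controls, if the follow-up SD is 3.5.* State the SD actually entered and its source, and stop equating the reduction from the current score with the difference between groups.

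Add a short table, labelled as assumptions, with the smaller net difference and the larger SDs shown above, both unadjusted and baseline-adjusted.

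The cost is a few sentences and a small table. The stated power becomes slightly less favourable. Recruitment targets, conduct and analysis do not change.

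### The drop-out allowance falls slightly short: 120 per arm less the expected 20% leaves 96, below the stated minimum of 99 (a minor inconsistency, about 1 point of power)

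*Protocol article*

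**What the plan says.** All the figures stand in one paragraph of the protocol article, under Sample size calculation. The effect is a fall in mean AUDIT score from 12: "it is assumed that the intervention will reduce the current AUDIT score by 12% to 10.6". The power claim is that "the estimated sample size will allow us with 80% power (5% level of significance) to detect the difference of 12% between the two groups". The number needed follows: "This will give a minimum of 99 patients per arm". Attrition comes next: "It is expected that 20% of participants may be lost prior to completing the 3-month and 12-month follow-up assessments". The same sentence then draws the recruitment figure from it ("follow-up assessments so that the final sample would be 120 per arm"), and the paragraph closes with the total, "A total of 240 HIV patients". No standard deviation is given; the only description of the method is "The sample size was calculated using Open Epi".

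The Data analysis section bears on what happens to patients who are lost. It plans a 2×3 repeated-measures analysis of variance for the alcohol score, with multiple imputation (five datasets) of missing values at baseline, 3 months and 12 months.

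**The concern.** The paragraph presents 120 per arm as the result of allowing for 20% loss from a requirement of 99. A reader who applies the 20% to the 120 gets fewer than 99. The enrolment figure therefore fails to secure the minimum that the same paragraph sets, and the 80% power attached to that minimum is slightly overstated at the attrition the plan itself expects. At stake is the internal consistency of the sample size justification; the trial's ability to answer its question is barely affected.

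**Working it through.** **Inputs from the Sample size calculation section:** minimum 99 per arm; expected loss 20% (read as the total loss by the end of follow-up); 120 recruited per arm, 240 in total; 80% power at the 5% level; AUDIT 12 falling to 10.6, a difference of 1.4.

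**Input not in the document:** the standard deviation (SD), back-solved below. The 5% level is taken as two-sided, which the protocol does not state.

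**1. Where 120 may come from.** Adding 20% to the requirement gives 99 × 1.20 = 118.8, which rounds up to 119 and, with further rounding, to 120. The document does not show this step.

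**2. What 20% loss requires.** Enrolment = required completers / (1 − loss) = 99 / 0.80 = 123.75, so 124 per arm and 248 in total. Check: 124 × 0.80 = 99.2.

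**3. What 120 delivers.** 120 × 0.80 = 96 per arm, 3 below 99. The largest loss that still leaves 99 is 1 − 99/120 = 17.5%.

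**4. SD implied by 99 per arm.** SD = difference × √(n/2) / (1.960 + 0.842) = 1.4 × √49.5 / 2.802 = 3.52. An SD of 3.50 also gives 99 after rounding up. With the exact 12% difference (1.44) the implied SD is about 3.6; with a one-sided test it is about 4.0 for a difference of 1.4.

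**5. Power at 99 and at 96 per arm**, for a complete-case comparison of two means. Normal approximation: power = Φ(difference/SD × √(n/2) − 1.960). At SD 3.52 and n = 96 this is Φ(2.759 − 1.960) = 78.8%.

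| Basis | n = 99 | n = 96 |
|---|---|---|
| Normal, SD 3.52 | 80.0% | 78.8% |
| Normal, SD 3.50 | 80.4% | 79.1% |
| t distribution, SD 3.52 | 79.6% | 78.4% |
| t distribution, SD 3.50 | 80.0% | 78.7% |

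A difference of 1.44 with its own implied SD gives the same normal-approximation power at 96 (78.8%). A one-sided test with its own implied SD gives 78.9%.

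**6. Sensitivity to the unstated SD** (difference 1.4, two-sided, normal approximation).

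| SD | n = 99 | n = 96 |
|---|---|---|
| 3.0 | 90.7% | 89.9% |
| 3.5 | 80.4% | 79.1% |
| 4.0 | 69.2% | 67.9% |
| 5.0 | 50.4% | 49.2% |

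Going from 99 to 96 costs 0.8 to 1.3 points at every SD shown. The absolute power depends far more on the SD than on the three patients per arm.

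**The case against.** The best defence is that this does not matter. Attrition is a forecast, the protocol words it tentatively, and three patients per arm lie well inside the error of any such forecast. The Procedure section plans repeated contact attempts, including renewed attempts at the next visit after a missed one. The Data analysis section imputes missing values, so patients who drop out stay in the analysis set and 96 is not strictly the number analysed. The powers above are for a complete-case comparison at one time point, which is not the planned analysis of the alcohol score.

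Much of this stands, and it is why the point is minor. It does not remove the inconsistency. Imputation does not fully restore outcome information that was never collected, and by inflating for loss at all the plan itself treats dropout as costly. Nor can 120 be read as the number left after loss, because the 240 are the patients to be recruited.

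Three stronger readings are tempting, and the document does not support them:

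- *The trial is underpowered, or must enrol eight more patients.* A loss of about 1 point does not bear that out.
- *The plan multiplied by 1.2.* This fits the figures but is an inference, since the protocol does not show how 120 was reached.
- *Adjusting for baseline would make good the shortfall.* The Data analysis section names no baseline-adjusted model, and the protocol gives no correlation between baseline and follow-up scores, so no recovered power can be claimed.

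**Conclusion.** The point holds as a minor arithmetic inconsistency. At the plan's own 20% loss, 120 per arm leaves 96 rather than the required 99; 20% loss would call for 124 per arm (248 in total), and 120 covers 17.5%. This part needs no assumption beyond the protocol's figures.

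The effect on power is about 1 point, to roughly 78 to 79%. That figure rests on an SD of about 3.5, which is inferred from the 99 and not stated, and on a complete-case comparison of two means. With the planned imputation the true cost may be somewhat smaller.

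**What to change.** Replace the attrition sentence with wording such as: 120 per arm retains at least 99 evaluable patients per arm if loss does not exceed 17.5%; with 20% loss 96 per arm remain, giving about 79% power under the assumed SD. State that SD and its source, because the 99 cannot be reproduced without it.

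The cost is one corrected sentence and a marginally less favourable power statement. Recruitment was already under way according to the Trial status section. No added enrolment or change to the analysis is needed.
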